**Treatment**

**Drugs**

Ixekizumab (*Eli Lilly and Company*): 80 mg/ml, 160 mg as a single hypodermic injection.

Antiviral treatment: according to the diagnosis and treatment plan for pneumonia related to infection by novel coronavirus of the Health Commission (trial version 6 and update).

**Treatment Protocols**

After the subjects sign the informed consent form, the researchers will complete the evaluation within 2 days.

The first phase: open design. Three subjects are enrolled in the same center. They are given ixekizumab and antiviral therapy (aerosol inhalation of α-interferon, lopinavir/ritonavir, chloroquine, ribavirin, or arbidol but not more than 3 types). The vital signs and changes in disease, inflammation indexes (CRP, IL-6, TNF-α) and infection indexes (routine blood tests) are monitored. Changes in PCT and immune function (T cell subsets) are detected. If there are no serious drug-related safety events in the patient's condition, the results of the first stage will be reported to the ethics committee for evaluation and approval, and the second phase of the study will be carried out.

In the second stage, 40 subjects are randomly divided into two groups at a 1:1 ratio. They are given ixekizumab and antiviral therapy (aerosol inhalation of α-interferon, lopinavir/ritonavir, chloroquine, ribavirin, or arbidol but not more than 3 types) or antiviral therapy alone. The course of treatment is 14 days. The vital signs, blood oxygen saturation, CT and other related indexes are followed up on days 0, 3, 7, and 14. The changes in inflammation indexes (CRP, IL-6, TNF-α), infection indexes (blood routine, PCT) and immune function (T cell subsets) and other indexes are monitored. The last follow-up is completed on the 14th day or early recovery and discharge (Figure 2).

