**Strengths and limitations of this study**

This trial protocol first describes a pilot-randomized, evaluator-blind, and controlled clinical trial testing the safety and efficacy of ixekizumab and antiviral treatment in patients with COVID-19.

Possible limitation was that the sample size was not statistically estimated.

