**Eligibility Criteria**

The inclusion criteria for the trial are as follows: the age is 18-75 years old, regardless of sex; COVID-19 will be diagnosed by RT-PCR or gene sequencing; the clinical types are common type (including severe high-risk factors) (multiple lesions of both lungs, or lung imaging showing that the lesion progressed more than 50% within 24 to 48 hours) and severe type; an increase in IL-6 levels; and the patient voluntarily signing the informed consent form.

The exclusion criteria for the trial are as follows: severe new pneumonia infection with one of the following conditions: respiratory failure requiring mechanical ventilation, shock, ICU monitoring and treatment with other organ failure; allergy to ixekizumab or antiviral drugs; ALT/AST>5 times the ULN, neutrophils<0.5 × 10^9/^L, or platelet less than 50 × 10^9^/L; patients with impaired renal function: serum creatinine ≥2 mg/dl (176 μmol/l); complications with severe underlying diseases or a life expectancy of less than 3 months; patients with active hepatitis, definite severe bacterial or fungal infections, tuberculosis infection, or HIV infection; malignant tumors, such as lymphoproliferative diseases; active Crohn's disease; pregnant or lactating women; participation in other intervention clinical trials in the past 3 months; or other situations in which the researchers believe that it is not appropriate to join the group.

The termination standards for the trial are as follows: allergy to research drugs; judgment of the researchers that it is necessary to terminate the study ahead of time because continuing to participate in the study may bring unacceptable risks to the subjects' health based on the occurrence of serious adverse events, or the subjects are unwilling to continue to participate in the study because of the adverse events; the observation of the curative effect was affected by other diseases such as stroke in the trial; or the ethics committee or regulatory body requested that the study be suspended.

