**Randomization**

The first stage is an open design. In the second stage, central randomization is used, and the eLite random system of Nanjing Medical University is used. The main efficacy indicator CT results will be evaluated by the third-party blind method outside the research team.

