**Baseline Procedures**

The following assessments must be completed during the screening period: medical history, occupational history, drug history, hobbies and smoking history; vital signs: respiratory rate, heart rate, and blood pressure; clinical symptom evaluation: dyspnea score; routine laboratory examination: routine blood tests, routine urine tests, liver and kidney function, blood glucose, electrolytes, troponin, serum ferritin, CRP, IL-6, TNF-α, PCT and T cell subsets; arterial blood gas analysis: pH, PaO2, PaCO2 and oxygenation index; routine electrocardiographic examination (ECG); chest high-resolution CT (HRCT) examination and score; and APACHE II score.

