**Enrollment and follow-up**

Those who meet the enrollment criteria will enter the intervention:

On the 3rd day of enrollment, the following procedures will be performed: (1) record concomitant medication; (2) record adverse events; and (3) carry out CT examination.

On the 7th day (±1 day)), the following procedures will occur: (1) record the combined use of drugs; (2) record adverse events; (3) measure vital signs: respiratory rate, heart rate and blood pressure; (4) evaluate clinical symptoms: dyspnea score; (5) perform routine laboratory examination: routine blood, routine urine, liver and kidney function, blood glucose, electrolyte, troponin, hypersensitive CRP, procalcitonin, serum ferritin; (6) assess inflammation index (CRP, IL-6, TNF- α), infection index (routine blood tests, PCT) and immune function (T cell subsets); (7) analyze arterial blood gas: pH, PaO2, PaCO2 and oxygenation index; (8) perform HRCT examination and score; and (9) calculate APACHE II score.

Fourteen days after admission (±3 days) or discharge, (1) record the combined use of drugs; (2) monitor possible adverse reactions to ixekizumab; (3) check vital signs: respiratory rate, heart rate, blood pressure; (4) evaluate clinical symptom: dyspnea score; (5) perform routine laboratory examination: routine blood, routine urine, liver and kidney function, blood glucose, electrolyte, troponin, hypersensitive CRP, procalcitonin, serum ferritin; (6) assess inflammation index (CRP, IL-6, TNF-α), infection index (routine blood, PCT) and immune function (T cell subsets), and so on; (7) analyze arterial blood gas: pH, PaO2, PaCO2 and oxygenation index; and (8) perform HRCT examination and score; (9) APACHE Ⅱ score was calculated (Figure 1).

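### In stage 2, staff who know the arm choose the background antivirals, and nothing fixes that choice before the allocation is known

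*Protocol*

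**What the plan says.** Stage 2 randomises 40 patients 1:1 to ixekizumab plus antivirals or to antivirals alone (Protocol, Treatment Protocols). The antiviral list opens with inhaled α-interferon and continues "lopinavir/ritonavir, chloroquine, ribavirin, or arbidol but not more than 3 types) or antiviral therapy alone". That makes five agents, at most three per patient. Treatment, Drugs ties the antivirals to the national treatment plan, trial version 6 and updates. Cointerventions, Permissible combination also allows antiviral treatment and cites trial version 5.

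On blinding, Strengths and limitations describes a "pilot-randomized, evaluator-blind, and controlled clinical trial", and Sample Size Projections calls the study open. Randomization says "The main efficacy indicator CT results will be evaluated by the third-party blind method outside the research team". No placebo is described. On allocation, the same section says "central randomization is used, and the eLite random system of Nanjing Medical University is used", with nothing about entering a treatment choice first.

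On records, Baseline Procedures lists "medical history, occupational history, drug history, hobbies and smoking history" at screening. Enrollment and follow-up asks for concomitant medication on day 3, and on day 7 and day 14 (or discharge) staff "record the combined use of drugs".

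**The concern.** In an add-on trial both arms should get the same background treatment apart from chance. A clinician-chosen background is legitimate, and the contrast then estimates ixekizumab added to usual antivirals, provided the choice does not depend on the arm. Here the choice can be made, or changed, by people who know the arm. A clinician might add an agent for a control patient who seems under-treated, or hold one back from an ixekizumab patient for fear of reactions. Either would be understandable, and either would make the arms differ by more than ixekizumab.

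Two outputs are exposed. Security Analysis compares adverse event counts and incidence between the groups; antivirals can cause reactions themselves, so this comparison can shift even if no antiviral works. The primary outcome, change in CT score, is exposed only if the antivirals affect CT. Blind reading protects how the scan is scored, not what the patient was given.

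**Working it through.** The plan's only sample size figure is 43 = 3 (stage 1) + 40 (stage 2). It gives no effect size, SD or power, so no bias can be computed from it. The check is mainly a comparison of sections.

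**1. Do prescribers know the arm?** One arm receives an injection and the other has no described placebo. Three sections (Strengths and limitations, Randomization, Primary outcomes) place the blinding at the evaluator or the CT reading, and Sample Size Projections calls the study open. Nothing masks treating staff.

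**2. How wide is the choice?** On the list and cap alone, the permitted regimens number C(5,1) + C(5,2) + C(5,3) = 5 + 10 + 10 = 25. This is an upper bound, because the national plan may rule some out and its content is not in the protocol. Regimens can differ completely: one patient may take three agents and another the remaining two (3 + 2 = 5), sharing none.

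**3. Is the choice fixed before allocation?** In time order:

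| Step | Drug information recorded | Relation to allocation |
|---|---|---|
| Screening | Past drug use | Before; covers drugs already taken, not those intended |
| Central randomisation | None stated | At allocation |
| Day 3 | Concomitant medication | After |
| Day 7 (±1) | Drugs in combination | After |
| Day 14 (±3) or discharge | Drugs in combination | After |

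No row holds the intended regimen.

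**4. How would a difference reach the results?** For one agent, on a simple additive model,

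bias in the between-arm contrast = D × g,

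where D is the arm-driven difference in the proportion using the agent, and g is that agent's effect on the outcome. The bias is zero if either is zero. The protocol gives neither. For CT, g may be small: the Introduction says that no specific treatment exists. For adverse events, g need not be zero. Eligibility Criteria excludes patients with "allergy to ixekizumab or antiviral drugs", which recognises that antivirals can cause reactions but says nothing about a difference between arms.

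**5. What can the follow-up records do?** They can show which drugs each arm received. They cannot show what would have been given had the arm been unknown, so they cannot separate the effect of a prescribing difference from that of ixekizumab.

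**6. Can analysis repair it afterwards?** The regimen received is a post-allocation variable, possibly influenced by the arm and by early response, so adjusting for it is unsound. Stratifying by full regimen is also unworkable if the choice is as wide as the list allows: 40 / 25 = 1.6 patients per regimen, or 20 / 25 = 0.8 per arm.

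**The case against.** The strongest reply is that this is a generic risk of any open add-on trial, that the study is a pilot with no statistical sample size, and that nothing in the protocol shows prescribing will differ by arm. The choice is bounded by a closed list, a cap and a national plan, and drug use is recorded at three follow-up visits. A realised imbalance can be read from those records without any test.

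Much of this stands. The risk is not shown to have materialised, the choice is not unlimited, and the records do describe what was given. What does not stand is that the matter can be left to analysis. When a co-treatment is chosen is part of treatment and randomisation procedure, and it can be settled only before allocation.

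Three stronger readings are tempting and not supported:

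- A reader might infer that the control arm is outside the list and cap, because the bracket follows the ixekizumab arm. The natural reading is that it covers both arms; the sentence only needs to say so.
- A reader might take the version 5 and version 6 citations as a source of bias. Both apply to both arms alike, so this is a minor wording point.
- A reader might expect a regimen named before allocation to allow adjustment for arm-dependent prescribing. It would not. Such a regimen is a baseline variable, balanced in expectation by randomisation; adjusting for it deals with chance imbalance, not with what staff do once they know the arm.

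**Conclusion.** The point holds as a correctable weakness of procedure. In stage 2, treating staff can know the arm, may choose up to three of five antivirals within the cited guideline, and are not asked to commit to a choice before the arm is released. Arm-dependent prescribing could enter the adverse event comparison and, if the antivirals affect CT, the primary outcome. Its direction and size are unknown and it may be zero. The documents do not support saying that the comparison is confounded or invalid; it remains valid if prescribing does not depend on the arm.

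The conclusion rests on one inference, that staff are unblinded in stage 2. The absence of any described placebo and the protocol's own labels make that a sound one. The change should be made because it is cheap and cannot be made after the fact, not because harm has been shown.

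**What to change.** 1. In Randomization, require the intended antiviral agents to be entered in the existing central system before the allocation is released.
2. In Treatment Protocols, state that the list and the three-agent cap apply to both arms.
3. Report every later change of antiviral by arm, with date and reason, against the regimen entered beforehand.
4. As a wording matter, cite one guideline version in Treatment, Drugs and in Permissible combination; which one is for the sponsor to settle.

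The cost is one data field and a short amendment. There is time for it, since Treatment Protocols already says "After the subjects sign the informed consent form, the researchers will complete the evaluation within 2 days". Sample size, follow-up and clinical freedom are unchanged. The limit is that staff may still change antivirals after allocation, so the step reduces and exposes arm-dependent co-treatment without removing it.

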**Secondary outcomes**

1) Pulmonary function prognostic indicators: percentage of subjects reporting each severity level (on a 7-point scale) (https://clinicaltrials.gov/ct2/show/NCT04280705). The scale is the assessment of clinical status at the first evaluation on a specified study day. The indicators are as follows: (1) death; (2) admission due to invasive mechanical ventilation or extracorporeal membrane oxygenation (ECMO); (3) hospitalization with noninvasive ventilation or high-flow oxygen equipment; (4) hospitalization requiring oxygen inhalation; (5) hospitalization without oxygen inhalation; (6) hospital discharge with limited activity; and (7) no need to be hospitalized and activities are not restricted.

2) Clinical symptom relief time: Clinical symptom relief is defined as normal body temperature for >72 hours (without taking antipyretic drugs or glucocorticoids) and no conscious dyspnea or relief of dyspnea.

3) The incidence of admission to the ICU on the 3rd day, 7th day and 14th day;

4) The incidence of noninvasive ventilation on the 3rd, 7th and 14th days;

5) 14-day etiological mortality and 14-day all-cause mortality;

6) Length of hospitalization;

7) Changes in troponin, inflammation indexes (CRP, IL-6, TNF-α), infection indexes (blood routine, PCT) and immune function (T cell subsets)) on the 7th and 14th days.

8) The ratio of arterial partial pressure of oxygen (PaO2) to fraction of oxygen inhalation (FiO2) on the 3rd, 7th and 14th days.

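### Follow-up may end at early discharge with no later contact planned, yet mortality, ICU admission and noninvasive ventilation are set at a fixed Day 14 and adverse event incidence is compared between arms

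*Protocol*

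**What the plan says.** Three parts of the protocol bear on when observation ends.

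- **Treatment Protocols, second stage.** Vital signs, CT and other indexes "are followed up on days 0, 3, 7, and 14". The same paragraph closes with "The last follow-up is completed on the 14th day or early recovery and discharge".
- **Enrollment and follow-up.** The final visit is timed as "Fourteen days after admission (±3 days) or discharge". The Day 3 procedures in the same section are counted from enrolment.
- **Secondary outcomes.** The list includes "14-day etiological mortality and 14-day all-cause mortality" and "The incidence of admission to the ICU on the 3rd day, 7th day and 14th day", with noninvasive ventilation on the same three days. None of these offers discharge as an alternative time. The seven-level status scale ends with "hospital discharge with limited activity; and (7) no need to be hospitalized and activities are not restricted". Its timing is given only as "The scale is the assessment of clinical status at the first evaluation on a specified study day".

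In addition, the Security Analysis section plans to summarise and compare adverse event incidence between the two groups. The Primary outcomes section, by contrast, builds discharge into the timing of the CT score.

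**The concern.** An outcome fixed at Day 14 needs each patient's status to be known at Day 14. Under the plan as written, a patient discharged on Day 8, say, has a last assessment on Day 8. Nothing is then scheduled that would show whether that patient died, entered an ICU, needed ventilation or had an adverse event in the remaining six days.

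The gap is not random. Patients leave observation because they recover, and recovery is what the treatment is meant to affect. If one arm goes home sooner, that arm has more unobserved Day-14 outcomes and less time in which adverse events can be recorded. It could then look safer partly because it was watched for less time. What is collected is settled by the protocol, so a statistical analysis plan could describe the gap but could not fill it.

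**Working it through.** No sample size or power calculation is given, so there is no planned figure to reproduce beyond the total: 3 + 40 = 43, which agrees with the protocol. The check is mainly a comparison of passages.

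**1. Is there any planned contact after discharge?**
- Treatment Protocols and Enrollment and follow-up both allow the last assessment to be made at discharge.
- The withdrawal text under Eligibility Criteria continues follow-up where possible, but only for patients who meet termination or withdrawal criteria. Discharge after recovery is not one of these.
- The section on reporting and follow-up of adverse events follows a bacterial or fungal infection until it has resolved or settled. It gives no means of detecting one that begins after discharge.
- Figure 2 lists Day 14 for both arms without exception, but the closing sentence of Treatment Protocols releases patients discharged early.

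No section plans a call, an outpatient visit or a record check.

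**2. Which outcomes are affected?**

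| Item | Timing in the protocol | Planned observation at Day 14 if discharged early |
|---|---|---|
| Primary CT score | Day 7; Day 14 or discharge | Not needed; discharge allowed |
| Etiological and all-cause mortality | 14 days | None |
| ICU admission | Days 3, 7, 14 | None |
| Noninvasive ventilation | Days 3, 7, 14 | None |
| Adverse event incidence by arm | No end day in Security Analysis | None after discharge |
| Seven-level scale | A specified study day | Level can be marked at discharge, but that is not Day-14 status |

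**3. Size.** Patients per arm: 40 / 2 = 20. One unseen death changes an arm's rate by 1 / 20 = 5 percentage points.

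The share discharged before Day 14 is not given, so the range below is an assumption. If a fraction f of an arm leaves early, 20 × f patients have no planned Day-14 status. With no observed deaths in that arm, its 14-day mortality is known only to lie between 0 and f.

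| f (assumed) | Patients per arm without Day-14 status | Possible 14-day mortality |
|---|---|---|
| 10% | 2 | 0 to 10% |
| 25% | 5 | 0 to 25% |
| 50% | 10 | 0 to 50% |
| 75% | 15 | 0 to 75% |

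These are logical bounds, not likely values. For a sense of likelihood, suppose 10 per arm (20 in all) leave early and each has a risk p of dying between discharge and Day 14. The chance of missing at least one death is 1 − (1 − p)^20. This gives 18% at p = 1%, 33% at p = 2% and 64% at p = 5%. Both the 10 per arm and the values of p are assumptions.

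For adverse events, a patient discharged on Day 7 contributes 7 / 14 = half the observation time of one followed to Day 14.

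**4. Time origin.** The last visit is counted from admission and the Day 3 visit from enrolment. If enrolment comes L days after admission, the nominal last visit falls on study Day 14 − L. With L = 2 (assumed; no lag is given) that is study Day 12. Day 14 is therefore not the same day throughout the schedule.

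**The case against.** The strongest reply is that the primary outcome is untouched, because the CT score may be read at discharge. The affected outcomes are secondary or safety outcomes in an exploratory trial of 40 randomised patients whose size was not statistically estimated. Nor does the protocol show how likely death or an ICU stay is within days of discharge for recovery. All of this stands, and it limits the weight of the point.

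It can also be said that the text is less settled than it looks. One sentence and Figure 2 list Day 14 for everyone, and the final-visit wording could be parsed as 14 days after discharge. That last reading would conflict with the closing sentence of Treatment Protocols, so the passages would still have to be reconciled.

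A reader might infer more than the documents support:

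- **That the two best scale levels cannot be observed.** They can be marked at the discharge assessment, and the scale names no Day 14. What cannot be known is whether that level still holds on Day 14.
- **That the visit window itself loses outcomes, because the last visit may come three days early.** The window is symmetric and mainly concerns patients still in hospital. Nothing says their deaths, ICU stays or ventilation would go unrecorded after the visit.
- **That length of stay is lost.** For patients discharged early it is fully observed. For those still in hospital at Day 14, the protocol does not say that the discharge date will not be taken from the record, and censoring can be left to an analysis plan.
- **That discharged patients will simply be counted as alive and free of events.** The protocol does not say how they will be handled.

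**Conclusion.** The point holds in a limited form. For patients discharged before Day 14, the protocol plans no observation of 14-day mortality, Day-14 ICU admission, Day-14 noninvasive ventilation or later adverse events. The gap depends on recovery and may therefore differ by arm. This follows from the protocol's text and needs no numerical assumption.

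The only firm figure is the sensitivity: 5 percentage points per unseen death in an arm of 20. The number of patients affected and the chance of a missed death rest on assumed discharge rates and risks. The point should be fixed, but it does not threaten the primary outcome. The mixed time origin is a smaller fault to correct in the same edit.

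**What to change.** Keep the discharge assessment. Add a sentence to Treatment Protocols and to Enrollment and follow-up: every randomised patient discharged early has one telephone or hospital-record check on or shortly after Day 14 from randomisation. It should record vital status (with cause if the patient has died), any ICU admission or ventilation, activity limitation and adverse events since discharge. Count all second-stage visits from one origin, preferably randomisation, and bring the two sections and Figure 2 into line.

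The cost is at most 40 short calls or record checks, with no change in sample size. A call cannot supply the laboratory and blood gas values also listed for Day 14. For patients discharged early, those should be labelled as discharge values.
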